**3.6.2.1 dose adjustment of medication**

The management of toxicity involved supportive care, as well as prescheduled reduction in the dose of anlotinib, and interruptions of anlotnib dose until adverse events were tolerable (grade 2 or lower). Anlotinib could be reduced if patients had intolerable grade 2 or grade 3 treatment-related adverse events, which were judged by the investigators. The first dose-reduction of anlotinib was 10mg daily, the second dose-reduction of anlotinib was 8mg daily. If patients still could not tolerate to 8mg daily, anlotinib would be terminated. If anlotinib dose was reduced or interrupted, the dose could not be increases during subsequent cycles. Modifications to the sintilimab dose were not permitted. Patients who had intolerable adverse events (AEs) leading to the delay or cessation of one medication continued treatment with the other.

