**3.6.1 The use of Medication**

Eligible patients were given sintilimab intravenously at a dose of 200mg on day 1, and anlotinib orally at a dosage of 12mg daily from days 1-14 every 3 weeks. Treatment was maintained until progressive disease (PD), treatment intolerance, death, development of intolerable toxicity, or withdrawal of consent, with one cycle as 3 weeks.

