**3.6.2.3 Dose adjustment** **plan for next cycle**

| Table 1: Dose adjustment for treatment-related toxicity | |
| --- | --- |
|  | Grade 3-4 adverse events |
| Anlotinib | The drug was stopped until the toxicity was reduced to Grade 2, and then the dose was reduced to 10mg qd at first dose-reduction, further 8mg qd at second dose-reduction. If not tolerate to 8mg qd, then anlotinib was terminated. |
| Sintilimab | Modifications to the sintilimab dose were not permitted. Sintilimab could be stopped or re-challenged according to the instruction of immune-AE. |
| If the patient cannot recover after 21 days delay, the treatment should be withdrawn. According to NCI-CTCAE 5.0 | |

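### For a grade 3 treatment-related event, section 3.6.2.1 leaves anlotinib reduction to investigator judgement while Table 1 states it as a fixed step, so the same event can lead to different doses.

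*Protocol*

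**What the plan says.** Section 3.6.1 sets the starting dose: "anlotinib orally at a dosage of 12mg daily from days 1-14 every 3 weeks".

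Section 3.6.2.1 describes toxicity management as supportive care, scheduled reductions and "interruptions of anlotnib dose until adverse events were tolerable (grade 2 or lower"). Its next sentence gives the reduction trigger: "Anlotinib could be reduced if patients had intolerable grade 2 or grade 3 treatment-related adverse events, which were judged by the investigators". The steps follow: "The first dose-reduction of anlotinib was 10mg daily, the second dose-reduction of anlotinib was 8mg daily", with anlotinib ended if 8 mg is not tolerated. Reductions are one-way: "If anlotinib dose was reduced or interrupted, the dose could not be increases during subsequent cycles".

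Section 3.6.2.3 contains "Table 1: Dose adjustment for treatment-related toxicity". It has a single grade column, "Grade 3-4 adverse events", and the anlotinib row reads "The drug was stopped until the toxicity was reduced to Grade 2, and then the dose was reduced to 10mg qd at first dose-reduction", then 8 mg at a second reduction, then termination.

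Section 3.6.2, which introduces both, ties dose adjustment to severity and allows reduction or discontinuation for adverse events at any stage. It also says that a patient who needs more than two anlotinib reductions for toxicity should withdraw from the study. It gives no order of precedence between section 3.6.2.1 and Table 1.

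**The concern.** Section 3.6.2.1 and Table 1 cover the same drug, the same class of events (treatment-related toxicity) and the same dose steps. They are two statements of one rule, but they give that rule different force. In section 3.6.2.1 the reduction is permitted and rests on the investigator's view of the event. In Table 1 it is the stated sequel to stopping.

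The decision cannot be undone. A patient reduced under one reading stays at the lower dose for all later cycles and has used one of the two reductions available. A patient not reduced under the other reading has neither consequence. Safety is a stated objective in a trial of 28 planned patients, and its adverse-event data are read against the dose received. With two rules in force, it also cannot be said whether leaving a grade 3 patient at 12 mg follows the protocol or departs from it.

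**Working it through.** The plan gives no figure to reproduce here. The check sets the two texts side by side, followed by simple dose arithmetic.

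**Step 1: trigger and force, for a patient on 12 mg**

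| Event (treatment-related) | Section 3.6.2.1 | Table 1 | Conflict? |
| --- | --- | --- | --- |
| Grade 2, judged intolerable | Reduction to 10 mg permitted | No entry | Ranges differ; one text is silent |
| Grade 3 | Reduction permitted, investigator judges: 12 mg or 10 mg | Stop, then 10 mg | Yes: optional against fixed |
| Grade 4 | Not named in the reduction sentence; the interruption sentence still applies | Stop, then 10 mg | Ranges differ; one text is silent on reduction |

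Only grade 3 is named by both, and there the two texts give different sets of possible doses: {12 mg, 10 mg} against {10 mg}.

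**Step 2: does the result depend on how the trigger sentence is parsed?** *Intolerable* may qualify both grades or only grade 2.
- If it qualifies both, a grade 3 event judged tolerable falls outside the reduction sentence altogether, while Table 1 still reduces.
- If it qualifies only grade 2, every grade 3 event is inside the sentence, but the verb is still permissive and the decision is still the investigator's.

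The grade 3 conflict survives either parsing.

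**Step 3: the two uses of tolerable.** The interruption sentence in section 3.6.2.1 equates tolerable with grade 2 or lower. The next sentence provides for intolerable grade 2 events. Read literally, an intolerable grade 2 event already meets the condition that ends an interruption.

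**Step 4: size of one discrepant decision.** Inputs are the doses in sections 3.6.1 and 3.6.2.1.
- First step: (12 − 10) / 12 = 16.7% of the daily dose.
- Second step: (10 − 8) / 10 = 20% of the daily dose.
- Per cycle, assuming the 14-day schedule is kept at reduced doses: 12 × 14 = 168 mg, 10 × 14 = 140 mg, 8 × 14 = 112 mg. Each step is 28 mg per cycle, repeated in every later cycle.

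**Step 5: does other text settle it?** The general permission in section 3.6.2 to reduce for adverse events does not say when reduction is required. The heading of section 3.6.2.3 refers to the next cycle, but section 3.6.2.1 gives the same dose levels and itself speaks of subsequent cycles, so the two are not separated by time.

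**The case against.** The best defence is that the two texts are complementary: an optional reduction for intolerable grade 2, and stop-then-reduce for grades 3 and 4. The dose levels and the end point below 8 mg are identical in both. Much of this stands. A reader might infer that the texts contradict each other at grade 2 and grade 4 as well. The document does not support that, because at each of those grades one text is merely silent on reduction. Table 1 does not forbid a grade 2 reduction, and section 3.6.2 allows reduction for adverse events generally. For grade 4, the interruption until grade 2 or lower in section 3.6.2.1 agrees with Table 1's stop. The defence fails at grade 3, which section 3.6.2.1 names and makes discretionary.

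A second objection is that the same event need not produce different doses. That is right: an investigator who uses the option arrives at Table 1's 10 mg. The claim is that the doses can differ, not that they always will.

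A third objection is that the consequences are limited. Reduction and discontinuation rates are not stated endpoints; the safety endpoint is the incidence, type and grade of adverse events. The link from reductions to leaving the study rests on section 3.6.2 alone. Section 3.6.2.1 and Table 1 end anlotinib, and section 3.6.2.1 lets the other drug continue. Both limits are accepted.

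**Conclusion.** The point holds for grade 3 treatment-related events: reduction is discretionary in section 3.6.2.1 and fixed in Table 1, and nothing in the protocol says which prevails. The different grade ranges and the two uses of tolerable for grade 2 are further wording faults in the same rule, but they are not separate contradictions about dose.

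Each discrepant decision is worth one dose level (16.7% or 20% of the daily dose) for all later cycles, and one of the two reductions that section 3.6.2 allows before withdrawal. How often this would arise cannot be estimated, because the protocol gives no expected rate of grade 3 events. No effect on the response-rate decision rule or its error rates is shown or claimed. The conclusion assumes only that both texts are operative, which their shared scope and dose levels support. Correction is warranted because this is a live dosing rule, the decision is irreversible, and the repair is cheap.

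**What to change.** Reconcile section 3.6.2.1 and Table 1 into one rule. For each grade covered, state whether interruption is required or optional and whether reduction is required or optional. Put the rule in one place and have the other refer to it instead of restating it. Reconcile the two uses of tolerable and intolerable for grade 2 in section 3.6.2.1, so that the condition for ending an interruption and the condition for reducing the dose can both be applied to the same patient. The clinical content, including which grades require action, is for the sponsor to decide.

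The cost is an amendment to a few sentences and one table. No assessments, patients or analyses are added.

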**3.6.2.2 The necessary laboratory test results at the beginning of the next cycle of chemotherapy,**

- - - ANC count ≥1.5×109/L,
    - Platelet count≥80×10^9^/L,
    - Serum creatinine <1.5×ULN,
    - Serum total bilirubin≤1.5-times the upper limit of normal for patients without liver metastases; (3.0-times the upper limit of normal for patients without liver metastases)；,
    - AST/ALT ≤2.5-times the upper limit of normal for patients without liver metastases; (5.0-times the upper limit of normal for patients without liver metastases)

**3.6.2.3 Dose adjustment** **plan for next cycle**

| Table 1: Dose adjustment for treatment-related toxicity | |
| --- | --- |
|  | Grade 3-4 adverse events |
| Anlotinib | The drug was stopped until the toxicity was reduced to Grade 2, and then the dose was reduced to 10mg qd at first dose-reduction, further 8mg qd at second dose-reduction. If not tolerate to 8mg qd, then anlotinib was terminated. |
| Sintilimab | Modifications to the sintilimab dose were not permitted. Sintilimab could be stopped or re-challenged according to the instruction of immune-AE. |
| If the patient cannot recover after 21 days delay, the treatment should be withdrawn. According to NCI-CTCAE 5.0 | |

**3.6.3 Concomitant treatment**

**3.6.3.1** **Unallowed Treatment**

• Except for Anlotinib plus Sintilimab, no other anticancer drugs are allowed,

• Research drugs (e.g. research antibiotics, antiemetics, etc.).

• In the course of treatment, any Chinese herbal medicine treatment with anti-tumor as the indication.

• Radiotherapy, except palliative radiotherapy for existing bone metastases.

**3.6.3.2 Allowed Treatment**

• Unconventional treatment (such as non-anticancer Chinese herbal medicine treatment or acupuncture), vitamins/trace elements can be used without affecting the observation of the endpoint of the study, which is controlled by the researcher.

• Patients can receive palliative treatment and supportive treatment for the original disease, such as diphosphate treatment.

• In order to relieve symptoms, radiotherapy was performed on the existing bone lesions (bone metastases existing at baseline).

• Patients with known bone metastases at baseline and need radiotherapy should complete radiotherapy before the first use of the study drug.

• Patients who had bone metastases at baseline, but did not need radiotherapy before the first use of the study drug, and then needed radiotherapy during the study were allowed to receive radiotherapy.

• Patients with bone metastases received radiotherapy at baseline, and they can receive radiotherapy when they need radiotherapy in the subsequent study.

• For patients undergoing radiotherapy, irinotecan should be suspended until radiotherapy is completed and the toxicity related to radiotherapy has improved.

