**3.3.1 inclusion criteria**

- Patients have histologically or cytologically confirmed advanced or recurrent CRC;
- No prior systematic anti-cancer treatment and relapse or metastases was occurred more than 12 months after adjuvant chemotherapy;
- Patients have measurable disease as defined by RECIST 1.1 as determined by investigator;
- Patient with a history of radiotherapy at least 3 months before on the day of providing consent, but the measurable lesion should not be within the scope of radiotherapy;
- Patients with age of 18-75yr;
- Patients with a performance status of 0,1or 2 on the Eastern Cooperative Oncology Group.；
- Patients with Life expectancy of more than 12 weeks;
- Patients must have the ability to understand and sign the written informed consent voluntarily;
- Female of childbearing potential who are negative in a pregnancy test within 7 days before enrollment. Both male and female patients should agree to use an adequate method of contraception (total abstinence, an intrauterine device or hormone releasing system, a contraceptive implant and an oral contraceptive) starting with the first dose of study therapy through 120 days after the last dose of study therapy. Duration will be determined when the subject is assigned to treatment.

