• Patients with severe poor compliance or serious violation of the protocol;

• Pregnancy should be reported as a serious adverse event;

• Other diseases occurred in the course of the study. According to the judgment of the investigators, the disease will obviously affect the evaluation of the clinical situation of patients, and it is necessary to stop the treatment of this scheme;

• Patients develop a new malignant tumors that need treatment;

• Patients lost to follow-up;

• The use of prohibited drugs or other drugs that may lead to toxic reactions or bias the research results according to the judgment of researchers;

• The study drug treatment was suspended for more than 21 days;

• The patient died.

All patients who withdraw from the study should record the reason for withdrawal in the case report form and the patient's medical record.

All patients who withdraw due to adverse events or laboratory abnormalities should be followed up until the adverse events recover or stabilize, and the subsequent results of the events should be recorded. If any patient died during the trial or within 30 days after completion of the trial, the investigator should be informed. The cause of death must be recorded in detail on the serious adverse event (SAE) report form within 24 hours.

- 1. **Procedures**

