**3.6.2 Dose delay and dose adjustment of medication**

The toxicity of patients should be carefully monitored, and the dose should be adjusted according to the severity of adverse effect. It is suggested that the dose should be adjusted according to the most serious toxic reactions and laboratory abnormalities in the previous course of treatment or this course of treatment. The level of toxicity should be in accordance with NCI-CTCAE 5.0. If there are multiple toxic reactions, the dose should be adjusted according to the most serious toxic reaction.

The longest time allowed for treatment delay is 3 weeks, during which the symptoms should be relieved to CTCAE grade 1 or below. For patients with CTCAE grade 2 or more severe toxicity at baseline, symptoms should be reduced to baseline level.

Medication can be reduced / discontinued due to adverse events at any stage of the study.

If patients need to suspend treatment for more than 3 weeks due to treatment-related adverse reactions/toxicity, and the symptoms cannot be controlled even after the best supportive treatment, they should withdraw from the study.

If patients need to be hospitalized due to treatment-related adverse reactions / toxicities during the chemotherapy phase, all study drugs should be discontinued before all symptoms recover.

All adverse events should be graded according to NCI-CTCAE version 5.0.

If patients need to reduce anlotinib more than two times due to toxicity, they should withdraw from the study.

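### The only drug-hold instruction for on-study radiotherapy names irinotecan, which no patient may receive, so it applies to neither anlotinib nor sintilimab

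*Protocol*

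**What the plan says.** The regimen is fixed in Protocol section 3.6.1: "Eligible patients were given sintilimab intravenously at a dose of 200mg on day 1, and anlotinib orally at a dosage of 12mg daily", in 3-week cycles. Section 3.6.3.1 closes the list: "Except for Anlotinib plus Sintilimab, no other anticancer drugs are allowed". It also bars radiotherapy, apart from palliative treatment of bone metastases already known.

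Section 3.6.3.2 sets out that exception. Patients with bone metastases at baseline who did not need irradiation before the first dose but later "needed radiotherapy during the study were allowed to receive radiotherapy". For patients who need it at the outset, "Patients with known bone metastases at baseline and need radiotherapy should complete radiotherapy before the first use of the study drug". The section then gives its single instruction on drug treatment during irradiation: "For patients undergoing radiotherapy, irinotecan should be suspended until radiotherapy is completed and the toxicity related to radiotherapy has improved".

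Two other rules bear on this. Section 3.5 lists as a ground for withdrawal: "The study drug treatment was suspended for more than 21 days". Section 3.3.1 has the entry criterion on past radiotherapy: "Patient with a history of radiotherapy at least 3 months before on the day of providing consent".

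**The concern.** A hold during radiotherapy is a safety instruction. This one is tied to a drug that no patient on protocol treatment can be taking, so it cannot be carried out. The author plainly meant some treatment to be suspended, but the text does not say which.

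Three things are at stake: whether two investigational drugs overlap with irradiation, how adverse events arising in that period are attributed, and how drug exposure and time on treatment are recorded. Safety is one of the trial's stated objectives, so this goes beyond editing. If a study drug is held, the patient may also meet the withdrawal rule in section 3.5, and nothing links the two provisions.

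**Working it through.** No statistical figure is involved, so the check sets the provisions side by side.

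**Which drugs the hold reaches**

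- Drugs given (3.6.1): anlotinib and sintilimab.
- Drugs prohibited (3.6.3.1): every other anticancer drug, hence irinotecan.
- Drug named in the radiotherapy hold (3.6.3.2): irinotecan.
- Study drugs covered by the hold: none of the two.

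**Whether another provision fills the gap**

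- Section 3.6.2 governs delay, reduction and discontinuation for toxicity and adverse events.
- Section 3.6.2.1 governs interruption and reduction of anlotinib for adverse events, and lets one drug continue when the other is delayed or stopped for them.
- Table 1 in section 3.6.2.3 governs grade 3-4 adverse events.

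All three are triggered by toxicity. None is triggered by radiotherapy itself, so none supplies the missing instruction.

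**Whether the intended drug can be inferred**

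Putting the study drugs in place of irinotecan leaves three readings: hold anlotinib, hold sintilimab, or hold both. Because section 3.6.2.1 accepts one drug continuing without the other, a one-drug hold cannot be ruled out. The name looks carried over from another text. The table of contents lists a section 6.4 on irinotecan-related diarrhoea, while the body goes from 6.3 straight to 7. That suggests how the error arose; it does not show which reading was meant.

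**Link to the suspension limit**

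The hold in 3.6.3.2 ends when radiotherapy is finished and its toxicity has improved; no maximum length is given. Section 3.5 withdraws a patient after more than 21 days of suspension and names no cause. Section 3.6.2 ties its 3-week limit to treatment-related toxicity that cannot be controlled, and Table 1 speaks of failure to recover after a 21-day delay. A radiotherapy hold longer than 21 days falls under 3.5 on its plain words, but not under the toxicity-specific wording of 3.6.2.

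**Timing of radiotherapy before treatment**

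Section 3.3.1 counts back from consent; 3.6.3.2 counts to the first dose. Section 3.8.1 puts consent within the 28 days before the first dose. Radiotherapy that meets the 3-month criterion therefore ended at least 3 months before the first dose, and at least about 4 months before it when consent was taken 28 days ahead. Section 3.6.3.2 alone sets a minimum of 0 days.

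| Radiotherapy course | 3.3.1 | 3.6.3.2 |
| --- | --- | --- |
| Ended at least 3 months before consent | met | met |
| Ended before consent, under 3 months earlier | not met | met |
| Given after consent, ended before first dose | wording met | met |

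The third row shows that both rules can be satisfied together. The second shows where they diverge, and no exemption for palliative bone treatment is stated.

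**The case against.** The strongest reply is that this is leftover template wording in one contingent instruction, affecting a subset that may be empty, and that the toxicity rules still let the investigator reduce or stop medication for adverse events at any point. That limits the consequence, and it stands. It does not make the hold usable: those rules respond to toxicity once it has occurred, whereas the radiotherapy hold was meant to apply from the fact of irradiation.

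Several stronger readings are tempting, and the document does not support them.

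- **That both study drugs are to be continued through radiotherapy.** The protocol is silent on this; it does not say so.
- **That the hold is open-ended.** Its end is stated, though no maximum is.
- **That the 21-day rule leaves a radiotherapy hold wholly undecided.** Section 3.5 names no cause, so on a plain reading such a hold counts. What remains is to align it with the narrower wording elsewhere.
- **That the same patient is eligible under one section and ineligible under another.** Section 3.6.3.2 is a concomitant-treatment rule, not a waiver of an entry criterion. A patient irradiated shortly before consent fails 3.3.1, and nothing in 3.6.3.2 reverses that.
- **That the hospitalisation rule in 3.6.2 is equally inoperable because it refers to chemotherapy.** It says "during the chemotherapy phase, all study drugs should be discontinued before all symptoms recover". The protocol uses chemotherapy loosely for study treatment elsewhere too, and the rule expressly covers all study drugs, so it can be applied.
- **That practice will differ between sites.** There is one centre; any variation would be between investigators or between patients.

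**Conclusion.** The point holds in a limited form. The radiotherapy hold in section 3.6.3.2 is wrong as written: it names a drug outside the regimen that the protocol prohibits, applies to neither study drug, and no other provision replaces it. This rests only on the protocol's own text.

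The number of patients concerned is unknown. The protocol gives no rate of bone metastases or of on-study radiotherapy, so the documents support nothing narrower than 0 to 28. The response-rate hypotheses, the sample size, the stage boundaries and the error rates do not depend on this passage. The radiotherapy timing in 3.3.1 and 3.6.3.2 is a secondary matter of clarification, not a contradiction.

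**What to change.** Amend section 3.6.3.2 so that it agrees with 3.6.1 and 3.6.3.1. The sentence should refer to the drugs patients receive and state, separately for anlotinib and sintilimab, what the sponsor's clinicians intend during radiotherapy. The choice of rule is theirs; the requirement here is that the passages agree.

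In the same amendment:

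- make the sentence consistent with the 21-day suspension rule in 3.5 and with the toxicity-specific limits in 3.6.2 and Table 1, stating how a radiotherapy hold is treated under each;
- cross-reference the baseline bone-radiotherapy rule with the prior-radiotherapy criterion in 3.3.1, including whether that criterion is meant to apply to palliative bone treatment and from which date each interval runs.

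The cost is a few sentences in a protocol amendment. It needs no extra patients, visits or procedures, and no change to the statistical design.
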